## Secondary outcome measures

- Number of alcoholic drinks selected
- Number of non-alcoholic drinks selected
- Total number of drinks selected
- Proportion of total drinks selected that are alcoholic
- Number of alcohol units purchased
- Number of alcoholic drinks purchased
- Number of non-alcoholic drinks purchased
- Total number of drinks purchased
- Proportion of total drinks purchased that are alcoholic

**Table 1 Relative availability of non-alcoholic and alcoholic drinks displayed in the selection task**

|  | *Drink subset availability* | | |
| --- | --- | --- | --- |
| *Drink range* | *75% non-alcoholic, 25% alcoholic* | *50% non-alcoholic, 50% alcoholic* | *25% non-alcoholic, 75% alcoholic* |
| Beer, cider and soft drinks (n) | *Alcohol-free (AF) beer and cider (12)*  AF lager (4)  AF ale (4)  AF cider (4)  *Soft drinks (12)*  *Beer and cider (8)*  Lager (3)  Ale (3)  Cider (2) | *AF beer and cider (8)*  AF lager (3)  AF ale (3)  AF cider (2)  *Soft drinks (8)*  *Beer and cider (16)*  Lager (6)  Ale (6)  Cider (4) | *AF beer and cider (4)*  AF lager (2)  AF ale (1)  AF cider (1)  *Soft drinks (4)*    *Beer and cider (24)*  Lager (10)  Ale (8)  Cider (6) |
| Wine and soft drinks (n) | *AF wine (12)*  AF red wine (3)  AF white wine (5)  AF rose or sparkling wine (4)  *Soft drinks (12)*    *Wine (8)*  Red wine (3)  White wine (3)  Rose or sparkling wine (2) | *AF wine (8)*  AF red wine (3)  AF white wine (3)  AF rose or sparkling wine (2)  *Soft drinks (8)*    W*ine (16)*  Red wine (6)  White wine (6)  Rose or sparkling wine (4) | *AF wine (4)*  AF red wine (1)  AF white wine (1)  AF rose or sparkling wine (2)  *Soft drinks (4)*    W*ine (24)*  Red wine (9)  White wine (9)  Rose or sparkling wine (6) |

The drink type, brand, volume of container(s) (ml), alcohol strength (ABV), and price (£) of each drink selected and purchased will be recorded. The number of drinks will be recorded *per individual drink container* (i.e., a 4x330ml beer multipack will be recorded as four drink items).

Price promotions and variations for all drinks included in the selection task will be checked every month via Tesco.com and recorded. Prices shown in the task will reflect the full price on Tesco.com throughout the study.

## Additional measures

*Demographics*

Age, gender, and highest qualification attained (with the options: ‘Higher Education or professional / vocational equivalents’, ‘A levels or vocational level 3 or equivalents’, ‘GCSE / O Level grade A*‐C or vocational level 2 or equivalents’, ‘Qualifications at level 1 and below’, ‘Other qualifications: level unknown’, or ‘No qualifications’) (ONS, 2015).

*Household members*

Participants will be asked about the members of their household, including the number of adults (aged 18+) in their household who have been included for consideration in the drink selection and the number of children (aged <18) in the household.

*Drinking behaviour risk*

The Alcohol Use Disorders Identification Test (AUDIT) (Bohn, Babor, & Kranzler, 1995) questions will be used to assess the level of risk associated with participants’ drinking behaviour.

*Weekly unit consumption*

Participants will be asked to enter the number of drinks they have consumed and purchased over the previous seven days, which will be used to calculate the number of alcohol units.

*Open text comment*

Participants will be asked to provide comments on task, such as explaining their choice of drinks, via an open text box to inform future studies in this area.

**Refinement of study procedure**

We conducted a small test run of the study procedures (N=14) to identify any issues and collect feedback from participants, which was used to further develop and refine the study procedure and instructions, prior to the full study. The following measures were recorded but these test run data will not be included as part of the final dataset:

- Number of alcoholic units selected
- Number of alcoholic and non-alcoholic drinks selected and purchased
- Percentage exact matches, close matches (i.e., like-for-like swaps, based on drink type: such as alcoholic red wine, non-alcoholic beer), and non-matches between selection and purchasing
- Dropout rate from selection to purchasing task
- Average time to receive confirmation of delivery or collection slot and proof of purchase
- Average time to extract information from receipts
- Open ended feedback on participants’ experience completing the tasks

# Procedure

Participants will be recruited by a research agency (Roots Research: <https://rootsresearch.co.uk/>). They will be provided with a participant information sheet, instruction guide and a link to the study on the Qualtrics platform. The information sheet will explain the study and what they will be required to do. It will be made clear that they will be asked to purchase only the drinks that they select in the task (or like-for-like alternatives if they are out of stock) in their next grocery shop, and that the options may not include all of their usual brands. Before commencing the online study, participants will be presented with task instructions, as well as links to the participant information sheet and instruction guide for reference. They will then complete a tick-box consent page and be directed to the drink selection task.

Participants will be randomised to one of three drink subset availability conditions (Table 1). They will be shown two drink ranges of 32 options (64 drink items in total): i. beer, cider or soft drinks, and ii. wine or soft drinks, and asked to choose all the drinks they would like to purchase as part of their next online grocery shop at Tesco. Participants will be shown their total drink selection and price, and they will be given an opportunity to go back and amend their selection before continuing with the study. Then participants will be asked to provide their email address (to be entered twice to ensure accuracy) and answer questions regarding their demographics and typical drinking behaviour, and to briefly explain their drink choices. After completing the selection task, participants will be automatically sent an email detailing their selected drinks.

When participants complete the selection task, they will be prompted to check their email and provided with instructions to complete the purchasing stage of the study, alongside a link to the Tesco website. The instructions will also be included in the automatic email they are sent and will request that participants place all of their selected drinks in their online Tesco shopping basket, along with any other grocery items, book their delivery or collection slot and confirm their delivery or collection time and date within 48 hours, via a survey link in the email. Participants will be sent an email on the day of their delivery or collection with a request to send proof of purchase (i.e., a copy of their itemised receipt) to the research team within 48 hours. Up to two follow-up email reminders will be sent, two and four days after this time has lapsed. Researchers will record the drink information from the itemised receipts. Participants will be debriefed, including information about how they can find out more about the study and contact details for the research team, and reimbursed for their time participating in the study.

# Statistical plan

Analysis will be conducted in SPSS (version 24 or later) or similar packages.

A CONSORT flow chart will be produced to indicate the numbers approached, recruited and randomised to the various study arms.

## Primary outcome: Selection

A generalised linear model or similar - will be used to analyse the primary outcome (the number of alcohol units selected) between the three study arms. The reference group will be the 25% non-alcoholic, 75% alcoholic group, which is most representative of real world settings in which alcoholic drinks are more predominant than non-alcoholic drinks. Adjustment will be made for whether beer or wine was shown to the participant first (as a dichotomous random factor).

## Secondary outcomes

The above analysis will be repeated for most of the secondary outcomes. For the proportion of total drinks selected and purchased that are alcoholic we will use a binary logistic model based on the counts of drinks.

Each pairwise effect will be reported as a difference in means with 95% confidence interval (CI) of the mean, t statistics and p-values. For these pairwise comparisons only, a significant p value of 5%/3 will be adopted due to multiple comparisons. An umbrella p value and F statistic, between all three study arms, will also be reported.

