### *Sample size determination*

A previous online study compared the impact on drink selection of altering non-alcoholic vs alcoholic drink availability (Blackwell et al., 2020). The results showed that availability of non-alcoholic drink options affected drink selection (binary outcome of alcoholic drink selected, yes/no) in the online setting. The proportion of participants selecting an alcoholic drink decreased from 74% when non-alcoholic drink availability was low (25% of drink options), to 61% when availability was medium (50% of drink options), and 51% when availability was high (75% of drink options) (i.e., a difference of 13% and 10%, respectively, between adjacent groups). However, only a single drink was selected in this online study and there was no intention to purchase the selected drinks, or opportunity to do so. There is limited evidence available within the literature from which to estimate the effect of the intervention on selection behaviour of multiple drink options with the intention to purchase where the outcome is units of alcohol.

A maximum sample size of 600 is possible with available resources. Assuming a sample size of 600 is recruited and allowing for attrition of 15%, this would result in 510 participants (170/group) in the analysis dataset. Based on the primary outcome of the amount of alcoholic units selected, for a two group t-test with alpha of 5% and power 80% an effect size of 0.3 could be detected. Using data from the test run (~5/group) the conservative estimate of the SD is 12.1 (i.e. the maximum group variance observed). This suggests a difference of at least 3.7 units alcohol selected between groups may be detected by a linear regression model.

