## Randomisation

The study will be delivered on the Qualtrics platform, which will use an algorithm to randomise participants into one of the three conditions.

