# Intervention

## Availability of non-alcoholic and alcoholic drinks

Participants will view: i. a range of beers, ciders and soft drinks, and ii. a range of wines and soft drinks. These two drink ranges will each show 32 drink options (Table 1). The full list of possible drinks displayed across conditions can be found in Appendix A. The order in which the two drink ranges (beer, cider and soft drinks first or wine and soft drinks first) are presented will be randomised. In each range, the drink options within the three sub-categories (i.e., i. beer and cider, alcohol-free beer and alcohol-free cider, or soft drinks, ii. wine, alcohol-free wine, or soft drinks) will be presented together under their respective headings but their order of presentation will be randomised. The relative availability (proportion) of non-alcoholic (alcohol-free beer, cider or wine alternatives and soft drinks) and alcoholic (beer, cider or wine) drink options – and therefore alcohol units – will vary according to the three conditions. Alcohol-free beer, cider and wine will be clearly labelled to ensure that they are not confused with alcoholic drinks. Each drink option presented will be a different brand, i.e., as the relative availability of non-alcoholic drink options increases, there will be a larger choice of brands from which to choose. Drink images will all be shown as bottles or cans, either as single items or multipacks, depending on the availability of products at Tesco. Participants will be able to select as many drinks as they would like to purchase in their household grocery shop.

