| **San Pellegrino Aranciata Rossa 6 Pack Can 330Ml** | **n/a** | **6X330ml** | **£3.79 (£0.19/100ml)** | **n/a** |
| **Oasis Summer Fruit 1.5 Litre Bottle** | **n/a** | **1.5l** | **£1.00 (£0.07/100ml)** | **n/a** |
| **Schweppes Soda Water 1 Litre** | **n/a** | **1l** | **£1.50 (£0.15/100ml)** | **n/a** |
| **London Essence Orange & Elderflower Tonic 6 X 150Ml** | **n/a** | **6X150ml** | **£3.25 (£0.36/100ml)** | **n/a** |
| **Schweppes Canada Dry Ginger Ale 1Ltr** | **n/a** | **1l** | **£1.50 (£0.15/100ml)** | **n/a** |
| Bottlegreen Elderflower Presse 75Cl | n/a | 750ml | £2.49 (£0.33/100ml) | n/a |
| J20 Apple & Raspberry 275Ml X 6 | n/a | 6x275ml | £6.00 (£0.36/100ml) | n/a |
| Fever-Tree Indian Tonic Water 8 X 150Ml | n/a | 8 X 150Ml | £4.25 (£0.36/100ml) | n/a |
| Tesco No Added Sugar Ginger Beer 4 X 330Ml | n/a | 4 X 330Ml | £0.99 (£0.08/100ml) | n/a |
| ***Beer*** | | | | |
| **Heineken 12X330ml Bottles** | **5.00%** | **12x330ml** | **£11.00 (£2.78/l)** | **Y** |
| **Peroni Nastro Azzurro 4X330ml Bottles** | **5.10%** | **4x330ml** | **£6.50 (£4.93/l)** | **Y** |
| **San Miguel 4X330ml** | **5.00%** | **4x330ml** | **£4.50 (£3.41/l)** | **Y** |
| **Becks Lager Beer 20 X 275Ml** | **4.00%** | **20x275ml** | **£10.00 (£1.82/l)** | **Larger multipack** |
| **Budweiser 15 X 440Ml** | **4.50%** | **15x440ml** | **£12.00 (£1.82/l)** | **Addition** |
| **Stella Artois Premium Lager 4 X 568Ml** | **4.60%** | **4x568ml** | **£5.39 (£2.38/l)** | **Addition** |
| Fosters 4X440ml | 4.00% | 4x440ml | £3.49 (£1.99/l) | Addition |
| Carling Lager 18X440ml | 4.00% | 18x440ml | £9.99 (£1.27/l) | Addition |
| Amstel Lager Beer Can 4 X 440Ml | 4.10% | 4x440ml | £4.00 (£2.28/l) | Addition |
| Guinness Draught 4X440ml | 4.10% | 4x440ml | £4.49 (£2.56/l) | Addition |
| **Brewdog Punk Ipa 4X330ml** | **5.40%** | **4x330ml** | **£6.00 (£4.55/l)** | **Y** |
| **Hoegaarden White Beer 4X330 Ml Bottles** | **4.90%** | **4x330ml** | **£4.50 (£3.41/l)** | **Y** |
| **Adnams Ghost Ship 500Ml** | **4.30%** | **500ml** | **£1.70 (£3.40/l)** | **Y** |
| **Sharps Doom Bar 500Ml** | **4.30%** | **500ml** | **£1.49 (£2.98/l)** | **Y** |
| **Hobgoblin Ipa 500Ml** | **5.30%** | **500ml** | **£1.70 (£3.40/l)** | **Addition** |
| **Old Speckled Hen Can 4 X 500Ml** | **5.00%** | **4x500ml** | **£4.29 (£2.15/l)** | **Addition** |
| Abbot Ale Strong Bitter 4X500ml Cans | 5.00% | 4x500ml | £4.49 (£2.25/l) | Addition |

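### The logistic model for the two proportion outcomes counts containers as independent, so its standard errors would be too small

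*Protocol*

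**What the plan says.** The protocol's Secondary outcomes section (under Statistical plan) repeats the primary analysis for most secondary outcomes but makes an exception for the two proportions: "we will use a binary logistic model based on the counts of drinks". The outcomes concerned are listed under Secondary outcome measures as "Proportion of total drinks selected that are alcoholic" and "Proportion of total drinks purchased that are alcoholic".

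The text below Table 1 defines the count per individual container, so that "a 4x330ml beer multipack will be recorded as four drink items". The Intervention section sets no limit on the number per person: "Participants will be able to select as many drinks as they would like to purchase in their household grocery shop". Appendix A includes packs as large as "Becks Lager Beer 20 X 275Ml".

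Under Randomisation, the platform uses an "algorithm to randomise participants into one of the three conditions". No participant effect, dispersion parameter, robust variance or other allowance for repeated containers is named. The only random factor mentioned is whether beer or wine was shown first.

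**The concern.** A binary logistic model on counts takes its variance from the binomial distribution: each container is one independent trial. That fails here in two ways. Containers in a multipack share the same alcoholic or non-alcoholic value by construction, so one selection of the 20-bottle lager adds 20 identical successes. In addition, a person's separate choices are likely to resemble each other. Randomisation supplies about 170 independent units per arm, not the thousand or more containers those people choose.

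At stake are the confidence intervals and p-values for both proportion outcomes. The pairwise threshold of 5%/3 corrects for three comparisons. It cannot make up for a standard error that is too small by a factor of two or more.

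**Working it through.** **The plan's own figure.** The sample size section states that "allowing for attrition of 15%, this would result in 510 participants (170/group) in the analysis dataset". 600 × 0.85 = 510, or 170 per group. The detectable effect is √(2/170) × (1.960 + 0.842) = 0.304 SD, and 0.304 × 12.1 = 3.68 units. The stated 0.3 and 3.7 reproduce. That figure concerns units selected, with one total per participant, so this point does not touch it. No figure is stated for the proportions.

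**Inputs.** From the protocol: 170 per arm, pairwise threshold 0.05/3 = 0.0167 (two-sided critical value 2.394), and the Appendix A pack sizes. Not given, so assumed: containers per participant (m), within-participant correlation (ρ), and the share of choices that are alcoholic.

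**Step 1: correlation with a constant count.** The true variance exceeds the binomial variance by the design effect DE = 1 + (m − 1)ρ. The standard error is too small by √DE, and the false-positive rate at 0.0167 is 2Φ(−2.394/√DE).

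| m | ρ | DE | √DE | False positives at 0.0167 |
|---|---|---|---|---|
| 5 | 0.1 | 1.40 | 1.18 | 4.3% |
| 12 | 0.05 | 1.55 | 1.24 | 5.4% |
| 12 | 0.1 | 2.10 | 1.45 | 10% |
| 12 | 0.3 | 4.30 | 2.07 | 25% |
| 12 | 0.5 | 6.50 | 2.55 | 35% |

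When the count varies between people around a mean of 12, simulation gives about 14%, 34% and 44% for ρ = 0.1, 0.3 and 0.5. The increase depends on the assumed spread of the counts.

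**Step 2: pack sizes alone, with no between-person correlation.** Take the 50% condition in Appendix A (products in bold), with every product of a type equally likely and 60% of choices alcoholic.

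- Alcoholic: 32 products, pack sizes summing to 103 (mean 3.219), squares summing to 933 (mean square 29.156).
- Non-alcoholic: 32 products, pack sizes summing to 108 (mean 3.375), squares summing to 648 (mean square 20.25).
- Containers per choice: 0.6 × 3.219 + 0.4 × 3.375 = 3.281. Alcoholic share of containers: P = 1.931/3.281 = 0.589.
- Actual variance contribution per choice: 0.6 × 29.156 × 0.411² + 0.4 × 20.25 × 0.589² = 2.96 + 2.81 = 5.77.
- Contribution if containers were independent: 3.281 × 0.589 × 0.411 = 0.795.
- Ratio: 5.77/0.795 = 7.26, and √7.26 = 2.69. False positives at 0.0167: 2Φ(−2.394/2.69) = 37%.

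The number of choices per person cancels. Changing the alcoholic share of choices from 40% to 80% moves the factor only from 2.81 to 2.58, and the false-positive rate from 39% to 35%. Simulation with 3 or 5 choices per person on average (about 10 or 16 containers) gave factors of 2.85 and 2.69, with false-positive rates of 41% and 35%.

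**Step 3: packs and preference together.** Adding between-person correlation of 0.2 to 0.4 to the same simulation raised the factor to 2.9–3.7 and the false-positive rate at 0.0167 to 41–53%.

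**Step 4: does the remedy work?** On simulated data of this kind, participant-clustered robust standard errors gave rejection rates of 3–7% at nominal 5%, and about 1.5–2% at nominal 1.67%.

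**The case against.** The strongest reply is that the protocol never says clustering will be ignored. It names a model and a data layout, and each participant contributing an alcoholic count out of a total count is a natural reading of it. Only the variance estimator is then open, and a detailed SAP is promised. The same section also promises t and F statistics, which more often accompany an estimated scale parameter than a fixed binomial one.

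Part of this stands. A reader might infer that the protocol commits to ignoring clustering; it does not, and the SAP could add a correction. But the named model has a defined variance, and that variance is wrong here. The primary model is worded to allow an alternative, and the per-protocol matching rules are expressly left to the SAP; the logistic model has neither allowance. The t and F statistics come with a difference in means, in wording that covers all the outcomes, so they fix no dispersion term.

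It also stands that the size rests on assumptions. A participant who buys only single bottles has no pack effect, and a few weakly related choices inflate the standard error by only about 1.2.

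A reader might further object to the weighting towards buyers of large packs. The protocol openly defines a drink as a container and the outcome as a share of drinks, so that weighting follows from the declared outcome. It is not an error.

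**Conclusion.** The point holds for the two proportion outcomes. As written, the model gives standard errors that are too small: by about 1.2 with few drinks and weak correlation, 2.1 with 12 containers and correlation 0.3, and 2.7 from Appendix A pack sizes alone. The false-positive rate per comparison at 5%/3 is then roughly 5% to 45% in place of 1.7%, and slightly above one half in the most extreme run. The pack-size result is the firmest because it needs no assumed correlation. It does assume equally popular products and a given share of alcoholic choices, though it changes little with the latter.

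Two stronger readings are not supported. One is that a spurious arm effect is likely: in nearly all scenarios the chance per comparison is below one half, and the true value cannot be known from the protocol. The other is that the trial's main result is at risk: two of nine secondary outcomes are affected, while the primary outcome and the sample size are not. This is a correction worth making before analysis, of moderate weight.

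**What to change.** Keep the logistic model on each participant's pair of counts (alcoholic, total) and state that the participant is the unit of analysis. Obtain standard errors from a participant-clustered sandwich estimator, for example a GEE. An independence working correlation leaves the container-weighted estimate unchanged. A quasi-binomial or beta-binomial model is an acceptable alternative. Apply the same rule to the selected and the purchased proportion.

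The container-weighted definition may stay. A fractional logit on each participant's own proportion, with robust standard errors, can be added as a sensitivity analysis, labelled as a different estimand because it weights people equally.

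The cost is a sentence or two in the Secondary outcomes section and wider intervals for these two outcomes. No further data are needed.

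### Pairwise tests are judged at 5%/3 but shown with 95% intervals, so the two can disagree; an F-gated closed test or Holm would keep the 5% guarantee with more power

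*Protocol*

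**What the plan says.** The protocol gives its rule for comparing arms under Secondary outcomes. On reporting: "Each pairwise effect will be reported as a difference in means with 95% confidence interval (CI) of the mean, t statistics and p-values". On significance: "For these pairwise comparisons only, a significant p value of 5%/3 will be adopted due to multiple comparisons". On the overall test: "An umbrella p value and F statistic, between all three study arms, will also be reported". No significance level is attached to the F test, and nothing makes the pairwise tests depend on it.

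The section on the primary outcome names the model and the reference arm but gives no pairwise significance level. The sample size section works at an unadjusted level: "for a two group t-test with alpha of 5% and power 80% an effect size of 0.3 could be detected". It adds that "the conservative estimate of the SD is 12.1" and concludes that "a difference of at least 3.7 units alcohol selected between groups may be detected by a linear regression model". It does not mention 5%/3.

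**The concern.** Two features of the pairwise rule deserve attention.

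First, a 95% interval corresponds to a 5% test, while the verdict is taken at 1.67%. A difference can therefore be reported with an interval that excludes zero and still be called not significant. The protocol does not say which of the two the reader should follow.

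Second, the protocol will compute an overall F test but gives it no part in the decision, and applies plain Bonferroni to each pair. With exactly three arms, procedures with the same family-wise guarantee reject more often. The trial has little power to spare: the protocol caps recruitment at 600, and the power statement was made at 5%. If the pairwise rule applies to the primary outcome, the power given there is not the power of the test that will be used.

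**Working it through.** **Inputs.** From Sample size determination: "this would result in 510 participants (170/group) in the analysis dataset", SD 12.1, alpha 5%, power 80%, effect size 0.3, difference 3.7 units. From Secondary outcomes: pairwise level 5%/3 = 1.67%, intervals at 95%. Assumed: two-sided tests (sidedness is not stated), equal arms, normal data, pooled variance with 510 − 3 = 507 degrees of freedom.

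**Step 1: the plan's own figure.** 600 × 0.85 = 510 = 3 × 170. The standard error of a pairwise difference is 12.1 × √(2/170) = 1.312 units. The detectable difference at two-sided 5% and 80% power is (1.960 + 0.842) × 1.312 = 3.68 units, or 3.69 with the t distribution. The stated 3.7 units reproduces, but only at an unadjusted 5%.

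**Step 2: the same figure at 5%/3.** The critical value rises from 1.960 to 2.394.
- Standardised difference: 3.7 / 1.312 = 2.819.
- Power at 5%: Φ(2.819 − 1.960) = Φ(0.859) = 80%.
- Power at 5%/3: Φ(2.819 − 2.394) = Φ(0.425) = 66%.
- Detectable difference at 80% power and 5%/3: (2.394 + 0.842) × 1.312 = 4.25 units.
- Keeping effect size 0.3 at 5%/3 needs 233 per arm: 699 analysable, and 699 / 0.85 = 823 recruited, against a maximum of 600.

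**Step 3: interval against verdict.** With 507 degrees of freedom:
- The 95% interval excludes zero beyond 1.965 × 1.312 = 2.58 units.
- The 5%/3 test rejects beyond 2.402 × 1.312 = 3.15 units.

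Observed differences between 2.58 and 3.15 units get conflicting answers. For a pair truly differing by 3.7 units the probability is the gap between the two powers, 80% − 66% = about 14%.

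**Step 4: is an adjustment needed?** Simulated family-wise error with all arms equal:
- three ungated 5% tests: about 12%
- Bonferroni: 4.4%
- F at 5%, then pairs at 5%: 5.0%
- Holm: 4.4%

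**Step 5: why the gated procedure is valid.** With three arms, if any two of the pairwise null hypotheses hold, all three do. The closed family therefore contains only the global null, tested by F at 5%, and the three pairwise nulls, each tested at 5%. When one arm differs, the single true-null pair was rejected in about 5% of simulated trials.

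**Step 6: pairwise power** (simulation, 3 × 170, SD 12.1):

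| True arm means (units) | Pair | Bonferroni | F-gated closed test | Holm |
|---|---|---|---|---|
| 3.7, 0, 0 | a pair that differs | 66% | 76% | 69% |
| 3.7, 1.85, 0 | extreme pair | 66% | 70% | 67% |
| 3.7, 1.85, 0 | adjacent pair | 16% | 28% | 20% |
| 7.4, 3.7, 0 | adjacent pair | 66% | 80% | 79% |

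**Step 7: does the mismatch go away?** Not fully. A 95% interval excludes zero in 80% of trials for a pair differing by 3.7 units. Under the gate the mismatch is 80% − 76% = about 4% when one arm differs, and 80% − 70% = about 10% for the extreme pair with equal steps. Under Holm the same subtractions give 80% − 69% = about 11% and 80% − 67% = about 13%.

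**The case against.** The strongest reply is that Bonferroni is a valid choice and that exchanging it for another valid procedure is a preference. Much of this stands. Without a gate, three 5% tests would err about 12% of the time, so some correction is required. The gain from changing is also uneven. With a total spread of 3.7 units, the extreme contrast rises only from 66% to 70%. The chance of declaring at least one pair different barely moves: 69% to 71% with equal steps, 81% to 84% with one arm different. The rise from 66% to 80% needs a total spread of 7.4 units.

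A second reply is that the aim is estimation, exact p-values will be given, and unadjusted 95% intervals are a conventional summary. That is fair, but the protocol does not call them unadjusted, and it sets a significance rule beside them.

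A third reply is that a detailed analysis plan is promised. That promise appears under the per-protocol analyses, and the mismatch is already fixed in the protocol's own wording.

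A reader might also infer that the Bonferroni tests are stacked on top of the F test and so penalised twice. The text does not say so: F is only reported alongside. Even as a gate it would cost Bonferroni under one percentage point.

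**Conclusion.** The point holds in a limited form. The interval level and the test level do not match, which affects observed differences of about 2.6 to 3.15 units and about 14% of trials for a pair truly differing by 3.7. Bonferroni is valid but less powerful than two alternatives with the same 5% guarantee. In the patterns examined, the gate gains 4 to 14 percentage points per pair and Holm 1 to 13.

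Three stronger readings are not supported. The correction is not needless, because without a gate some adjustment is required. The gate does not restore 80% power when the total spread is 3.7 units. Nor does it bring the 95% intervals fully into line with the verdicts, because they can still disagree when F is not significant.

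The effect on the primary outcome is conditional. The 5%/3 sentence sits under Secondary outcomes and is restricted to these pairwise comparisons. If it covers the primary outcome, the stated 80% power for 3.7 units is about 66%. If it does not, that loss disappears, but the protocol then states no multiplicity rule for the primary pairwise tests.

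The figures assume two-sided tests, 170 analysed per arm, a common SD of 12.1 and normal data. The SD comes from a test run of about five per group, so the thresholds in units are only as reliable as that estimate.

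**What to change.** Replace plain 5%/3 by one of two rules, and state that it covers the pairwise comparisons of both primary and secondary outcomes:

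- the overall F test at 5% as a gate and, if it is significant, each pair at 5%; or
- Holm across the three pairs, with no gate.

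Under either rule, label the 95% intervals as unadjusted for multiplicity.

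If the sponsor prefers to keep 5%/3, report 98.33% intervals, which are 2.394 / 1.960 = 1.22 times as wide. If it covers the primary outcome, also correct the sample size section: power is about 66% for 3.7 units, or the difference detectable with 80% power is about 4.25 units.

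The cost is a sentence or two in the analysis section and no extra participants. The price of the gate is that pairwise results are descriptive only when F is not significant. In the patterns examined, Bonferroni would have rejected a pair without a significant F in under 1% of trials. Holm has no such drawback, since it rejects everything Bonferroni rejects, but it usually gains less than the gate.
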